# TRanscutaneous lImb reCovEry Post-Stroke (TRICEPS): study protocol for a randomised, controlled, multiarm, multistage adaptive design trial

**DOI:** 10.1136/bmjopen-2024-092520

**Published:** 2025-03-26

**Keywords:** Stroke, Rehabilitation medicine, Clinical trials

## Abstract

**Introduction:**

Arm weakness after stroke is one of the leading causes of adult-onset disability. Invasive vagus nerve stimulation (VNS) paired with rehabilitation has been shown to improve arm recovery in chronic stroke. Small studies of non-invasive or transcutaneous VNS (tVNS) suggest it is safe and tolerable. However, it is not known whether tVNS paired with rehabilitation is effective in promoting arm recovery in chronic stroke and what the mechanisms of action are.

**Methods and analysis:**

TRICEPS is a UK multicentre, double-blinded, superiority, parallel-group, three-arm two-stage with an option to select promising arm(s) at 50% accrual, individually randomised, sham-controlled trial. Up to 243 participants will be randomised (1:1:1) using minimisation via a restricted, web-based centralised system. tVNS will be delivered by a movement-activated tVNS system (TVNS Technologies), which delivers stimulation during repetitive task practice. Rehabilitation will consist of repetitive task training for 1 hour a day, 5 days per week for 12 weeks. Participants will be adults with anterior circulation ischaemic stroke between 6 months and 10 years prior with moderate-severe arm weakness. The primary outcome measure will be the change in Upper Limb Fugl-Meyer total motor score at 91 days after the start of treatment. Secondary outcome measures include the Wolf Motor Function Test, the Modified Ashworth Scale to assess spasticity in the affected arm and the Stroke-Specific Quality of Life Scale. A mechanistic substudy including 40 participants will explore the mechanisms of active versus sham tVNS using multimodal MRI and serum inflammatory cytokine levels. Participant recruitment started on 30 November 2023.

**Ethics and dissemination:**

The study has received ethical approval from the Cambridge Central Research Ethics Committee (REC reference: 22/NI/0134). Dissemination of results will be via publications in scientific journals, meetings, written reports and articles in stakeholder publications.

**Trial registration number:**

ISRCTN20221867.

STRENGTHS AND LIMITATIONS OF THIS STUDYThis is, to our knowledge, the largest double-blinded, multicentre, randomised controlled trial of vagus nerve stimulation (VNS) in stroke.A closed-loop, movement-activated device allows the self-delivery of transcutaneous VNS at home with objective monitoring of treatment concordance.The trial has an efficient two-stage adaptive design. Prespecified stop-go criteria will allow continued enrolment to treatment groups where there is early promising evidence of efficacy and discontinuation of futile treatment groups.Participants with haemorrhagic stroke or posterior circulation ischaemic stroke are not eligible.This study will only address upper limb impairments poststroke.

## Introduction and rationale

Stroke is a leading cause of adult-onset disability.^1^ Up to 80% of stroke survivors experience arm weakness, and in 30%–60%, this persists at 6 months.^2^ Persistent arm weakness after stroke is a key driver of reduced independence, reduced employment and impaired quality of life (QoL).^1^ Rehabilitation is a key treatment in poststroke recovery. However, the rate and magnitude of the effect of active therapy are only partially restorative in chronic stroke (>6 months postonset).^3^ Novel strategies to increase the likelihood of arm recovery in chronic stroke are therefore a key priority for stroke survivors, clinicians and health services.

The vagus nerve provides bidirectional signalling between the brain and the body.^4^ In addition to being the output of the parasympathetic nervous system in the regulation of the heart and vasculature, it has key roles in the regulation of central and peripheral inflammation.^4^ Invasive vagus nerve stimulation (VNS) is well established as a treatment for medically refractory epilepsy.^5^ The VNS Rehabilitation (VNS-REHAB) study demonstrated that surgically implanted VNS temporally paired with rehabilitation therapy resulted in greater improvements in arm weakness than rehabilitation alone.^6^ The mechanism of this effect is likely to be cholinergic reinforcement, which increases task-specific plasticity in response to upper limb training. Several preclinical studies have shown that non-invasive transcutaneous VNS (tVNS), typically via the auricular branch of the vagus nerve (ABVN) at the cymba concha or tragus, activates vagus nerve projections centrally and improves upper limb outcomes in animal models of acute stroke.^7^ The potential advantages of tVNS over invasive VNS in stroke include the avoidance of safety risks from general anaesthetic and surgery, a lower overall cost, the ability to remove and redistribute the device from non-responders and the potential for use in the acute phase poststroke where invasive surgery is unfeasible.^8^ Pilot clinical studies have demonstrated that tVNS paired with rehabilitation can result in greater improvements in arm recovery in subacute and chronic stroke compared with sham stimulation.^9 10^ In a small unblinded pilot study, 12 participants with subacute chronic stroke completing a 6-week rehabilitation programme with concurrent tVNS had a mean 10.1-point increase in ULFM motor subscore.^11^ However, the efficacy of tVNS on arm recovery in chronic stroke and the relative effect size compared with invasive VNS is still not known. The mechanisms through which VNS may promote arm recovery in chronic stroke are not well understood, but it appears that VNS must be delivered during or immediately after limb movements to promote neuroplasticity.^4^ Furthermore, the activation of the central cholinergic pathways, specifically via the alpha-7 nicotinic acetylcholine receptors, may be a key mediator of the treatment effect.^4^ In a recent evaluation of ongoing clinical trials of tVNS in stroke, some key research gaps in tVNS and stroke have emerged.^12^ These include the absence of robust biomarkers of tVNS that can be used to evaluate the mechanism and optimise treatment dose and duration.^12^

## Study aims and objectives

The TRanscutaneous lImb reCovEry Post-Stroke (TRICEPS) trial aims to investigate the efficacy and mechanism of tVNS paired with upper limb rehabilitation on arm recovery in chronic stroke. The primary objective is to determine whether tVNS paired with self-delivered home rehabilitation therapy of the affected arm poststroke reduces arm motor impairment at 3 months from the start of treatment compared with self-delivered home rehabilitation therapy alone.

Secondary objectives are to determine: (a) whether the benefits of tVNS and self-delivered home rehabilitation therapy in reducing arm motor impairment observed at 3 months from the start of treatment are sustained; (b) whether tVNS and self-delivered home rehabilitation therapy improve other outcome measures related to sensory modalities, neurological deficit, QoL, depression, general anxiety, fatigue, pain, spasticity, strength and activities of daily living and (c) the safety of tVNS and self-delivered home rehabilitation therapy.

An imaging substudy will explore whether tVNS changes the cerebral representation of the affected arm, cerebral perfusion and functional connectivity and how they relate to reduced arm motor impairment.

## Methods

Critical details that could unblind or unmask the trial have been concealed while the trial is ongoing. A redacted version of the full protocol is available via https://fundingawards.nihr.ac.uk/award/NIHR133169. A full unredacted protocol with detailed methods will be accessible via this link when the study is completed. The core trial dataset is outlined in online supplemental table 1. A completed Standard Protocol Items: Recommendations for Interventional Trials (SPIRIT) checklist for the current manuscript is available as online supplemental appendix A.

## Trial design

TRICEPS is a multicentre, double-blinded, parallel-group, superiority, individually randomised, sham-controlled, three-arm, two-stage adaptive trial. This includes an internal pilot with a stop-go decision following 6 months of recruitment to assess feasibility (see Section 8.4 of the full protocol) and an interim analysis after the first stage to allow for the selection of promising treatment groups in the second stage as well as reassessing dropout rate and adjusting the sample size accordingly. Early trial stopping for efficacy has not been factored into the design. The flow diagram of the study design and participant interventions through the trial is summarised in figure 1.

**Figure 1 F1:**
[figure not shown]
Study flow diagram. AE, adverse event; mNIHSS, Modified National Institute of Health Stroke Scale; SS-QOL, Stroke-Specific Quality-of-Life; tVNS, transcutaneous vagus nerve stimulation; ULFM, Upper Limb Fugl-Meyer; WMFT, Wolf Motor Function Test; NEADL - Nottingham Extended Activities of Daily Living; mRS - Modified Rankin Scale; GAD-7 - General Anxiety Disorder Questionnaire 7; PHQ-9 - Patient Health Questionnaire-9; NFI-Stroke - Neurological Fatigue Index for Stroke; MAS - Modified Ashworth Scale; MRC - Medical Research Council; PET - Positron Emission Tomography.

### Patient population

Adults with anterior circulation ischaemic stroke between 6 months and 10 years previously with upper limb weakness.

### Inclusion and exclusion criteria

#### Inclusion criteria

Aged 18 years or greater.Anterior circulation ischaemic stroke (internal carotid, middle cerebral artery, anterior cerebral artery or anterior circulation lacunar stroke) between 6 months and 10 years previously.Baseline Upper Limb Fugl-Meyer (ULFM) total motor score of 20–50 (inclusive) indicating moderate to severe arm motor impairment.At least 10 degrees of active wrist extension, 10 degrees of active thumb abduction/extension and 10 degrees of active extension in at least two additional digits in the affected arm.Able to participate in active rehabilitation therapy, provide feedback on adverse events (AEs) and give informed consent based on clinical judgement.

#### Exclusion criteria

Has significant other impairment of the upper limb, for example, a frozen shoulder.Has severe spasticity (eg, as identified by the ULFM).Has other health conditions that prevent engagement with rehabilitation therapy, for example, advanced dementia.Has severe aphasia and either: (a) informed consent is unlikely based on the Consent Support Tool, (b) engagement with repetitive task training is difficult or (c) inability to communicate AEs from tVNS.Currently participating in another interventional stroke rehabilitation trial.Pregnant or trying to get pregnant.Has a pacemaker or another implanted electrical device.Has a cochlear implant or other similar device.Is currently receiving therapy or treatment to reduce arm motor impairment and would not be willing to stop for the duration of the trial.Has previously experienced a haemorrhagic stroke.Administration of botulinum toxin in the affected arm within the previous 3 months (participants must also be willing to not have further injections for the duration of the trial).

The entry criteria of a ULFM motor subscore of 20–50 is in line with the VNS-REHAB trial.^6^ This will enable a more direct comparison of the relative efficacy of invasive versus non-invasive VNS. The study team, including a patient and public involvement panel, felt that participants scoring <20 points on the ULFM may struggle to carry out repetitive task practice, thereby limiting the potential for meaningful gains, and those scoring >50 points on the ULFM have less impairment, and thereby the score may have a ceiling effect. The range of 20–50 aims to be as inclusive as possible while acknowledging the possibility of different trajectories of rehabilitation response according to stroke severity.^13^ The inclusion of participants from 6 months to 10 years poststroke is justified by previous work on intensive upper limb rehabilitation and was codesigned in consultation with stroke survivors. Spontaneous biological recovery is a prominent mechanism of recovery in the first 3–6 months poststroke, followed by a more stable chronic deficit.^14^ In the chronic phase (after 6 months), improvements in limb function are driven by rehabilitation, often delivered at high doses.^15 16^ Previous studies of intensive upper limb rehabilitation in stroke have shown improvements even several years poststroke onset.^16^

### Identification and recruitment

Potential participants will be identified through several possible routes. First, individual community stroke rehabilitation teams will be asked to identify participants under their active or historical care who meet the eligibility criteria. Second, individual sites will be asked to review records for potentially eligible stroke survivors via the Sentinel Stroke National Audit Programme database (routinely collected national audit record). Third, the trial will be advertised electronically via the trial website and social media advertisements and physically via posters in community rehabilitation and care settings with contact details of their local site and/or the central research team. Potential participants will be provided with an invitation letter and participant information sheet (online supplemental appendix B) via email or post. A telephone screening checklist outlining the core inclusion and exclusion criteria will be completed with the participant. A video screening assessment will be conducted where possible to determine the range of arm weakness and determine likely eligibility. Participants will be invited to an enrolment visit where they provide written informed consent for trial participation before completing the ULFM assessment. The consent form is shown in the online supplemental appendix C. If they meet the inclusion criteria, they will complete the remainder of the outcome assessments (as below) and proceed to randomisation; sites and participants will have the option to divide the baseline visit into two appointments if required. Participants who are eligible for the mechanistic substudy will be given an information sheet (online supplemental appendix D), and written informed consent (online supplemental appendix E) for participation will be required for participation in the substudy. Recruitment to the TRICEPS trial began on 30 November 2023.

### Randomisation

Eligible and consenting participants will be randomised using a centralised, validated, restricted, web-based randomisation system (SCRAM - Sheffield Clinical Trials Research Unit Randomisation System) hosted by the University of Sheffield Clinical Trials Research Unit (CTRU). Participants will be randomised 1:1:1 to one of three treatment groups using minimisation with a masked random probabilistic element to reduce the predictability of treatment allocation. A prespecified number of initial participants will be randomised using simple randomisation after which the randomisation will be minimised according to age (≤60, >60 years), baseline ULFM score (20–35, 36–50) and biological sex at birth (male, female) and by recruiting site to achieve good balance across treatment groups with respect to potential prognostic factors. The allocation ratio will be updated to 1:1, and the minimisation algorithm will be updated if a treatment is dropped at interim analysis.

### Blinding

Device set-up, device training and the therapy intervention will be delivered by unblinded team members. Depending on the site, only the research therapist (or research nurse) who will train participants on the use of the tVNS device will be unblinded. The CTRU data managers, trial manager and research assistant will also be unblinded to aid in operational aspects of the trial. All outcome assessments will be completed by a blinded trial outcomes assessor. TRICEPS uses a sham control device which will be the same as the active tVNS device, but the stimulation will be set at the minimum stimulation intensity level. Participants will be informed that they ‘may or may not’ be able to feel the stimulation from the device and that this varies between individuals. The research therapist or nurse will be provided with a script to guide this conversation and ensure all participants are given the same information to help maintain blinding. Emergency unblinding in case of a medical emergency or serious AE (SAE) will be permissible on an individual basis.

Participant-facing documents will be designed in such a way that potential participants receive enough information to be able to make an informed decision about participation but will not disclose too much about the difference between the treatment groups in order to preserve blinding. At the end of the 6-month intervention, participants will be asked whether they thought they were in the active or sham intervention; these results will be reported as an indicator of the blinding process.

Sheffield CTRU statisticians independent of the conduct of this trial will access unblinded data for monitoring purposes and to conduct interim analysis. They will communicate unblinded results to the DMEC. Trial statisticians will be blinded throughout the trial.

### Intervention

Participants will be randomised 1:1:1 to one of the treatment groups:

Group A: a treatment group that receives tVNS* with self-delivered rehabilitation (five times a week) for 12 weeks.Group B: a treatment group that receives tVNS* with self-delivered rehabilitation (five times a week) for 12 weeks.Group C: a treatment group that receives tVNS* with self-delivered rehabilitation (five times a week) for 12 weeks.

*The stimulation parameters (active or sham) and duration of tVNS use in the treatment groups are redacted from the current protocol to avoid potential unblinding of participants.

### tVNS device

All treatment groups will be given a wristband with a movement sensor (mbientlab), mobile phone and a tVNS stimulator with earpiece (tVNS Technologies). Participants will undergo device training at their first therapy visit, which will be supplemented with written and video-based training materials. Participants will wear the smart wristband during their therapy sessions, which will detect limb movement and trigger a pulse of tVNS via a preinstalled application on the provided mobile phone; this will enable the pairing of limb movement to stimulation (figure 2). The device will also record how long the device has been used and the number of motion-triggered stimulations.

**Figure 2 F2:**
[figure not shown]
tVNS system. (A) tVNS stimulator; (B) tVNS stimulation site at cymba concha; (C) smart wristband and mobile phone; (D) tVNS delivery during rehabilitation. Figures created by Morph. tVNS, transcutaneous vagus nerve stimulation.

The stimulator delivers tVNS to the ABVN at the cymba concha at 25 Hz and 0.1 ms pulse width. The intensity for group A will be set at 0.1 mA while for groups B and C, this will be set at a variable range between the individual participant’s minimum perceived threshold (minimum, at least 0.5 mA) and pain threshold (maximum, up to 5 mA). The mobile device provided will monitor adherence to intervention protocols. Participants will be able to modulate their intensity according to their tolerability on a day-to-day basis, but the device will not display the absolute intensity of the current. Negligible stimulation in the placebo group was chosen in order to maintain the functionality of the device and to minimise unblinding of participants.

### Rehabilitation

Each participant will be trained by a physiotherapist or occupational therapist to self-deliver therapy at home. Training will take place face-to-face in a clinical setting. The therapy will be tailored to the participant’s own set of functional impairments and based on the principles of repetitive task training.^17^ The aim is for approximately 7–10 tasks (such as turning cards, moving objects and opening/closing bottles) with 30–50 repetitions per task within a 1hour- session. A delegated unblinded research team member will contact the participant at 2-week intervals during the treatment period (12 weeks). The purpose of this contact is twofold; first, to identify any issues with rehabilitation therapy or the device; second, to progress the therapy as required.

### Primary and secondary outcome measures

Assessments and schedule of procedures are outlined in the online supplemental table 2 and figure 1. The primary outcome is the change in ULFM total motor score at 3 months from baseline (start of treatment). The ULFM total motor score consists of 33 items, each scored on a three-point ordinal scale (0, 1 or 2) with a range of 0–66;^18^ lower scores are associated with impaired function. All research staff carrying out the ULFM assessment will be trained and assessed with an accredited online programme. Further assessments that form the basis of secondary outcome measures are listed in full in online supplemental table 2 (schedule of procedures). These include the other components of the ULFM assessment (sensation, passive joint motion and joint pain), the Wolf Motor Function Test (WMFT),^19^ the Modified National Institute of Health Stroke Scale (mNIHSS)^20^ and the Stroke-Specific Quality-of-Life (SS-QOL) Scale.^21^ Training in the Wolf Motor Function Test will be carried out with video materials provided by the central team. Complete details of secondary outcomes are outlined in Section 8.2 of the full protocol.

### Trial monitoring and oversight

The day-to-day management of the trial will be supervised by the trial management group (TMG) and will meet at least monthly. The conduct of the trial will be overseen by the trial steering committee (TSC) and data monitoring and ethics committee (DMEC). The DMEC will meet regularly and review reports (blinded and unblinded) provided by the Sheffield CTRU to assess the trial progress, safety data and efficacy data to make recommendations on trial adaptations. They will advise the TSC who will also meet regularly to monitor the trial, review blinded data and act on DMEC recommendations on behalf of the funder and sponsor.

### Sample size justification and interim analysis

Rehabilitation alone has been shown to improve the ULFM total motor score by around 3 points^17^; an improvement of 6 points is considered the minimal clinically important difference (MCID).^22^ The active treatment group would need to improve the ULFM by 3 points more than sham tVNS and rehabilitation to be clinically meaningful. The trial will require 228 participants in total (76 per group) with ULFM outcome at 3 months. An interim analysis for treatment selection will be performed when 114 participants in total (38 per group) have accrued ULFM outcome at 3 months. This assumes a 1:1:1 allocation ratio, 85% marginal power and 2.5% one-sided family-wise type I error. We expect a 6% dropout rate,^16^ so the initial sample size is inflated to 243 participants (81 per group). However, this dropout rate will be re-estimated at an interim analysis, and the sample size adjusted accordingly to achieve 228 participants with primary outcome data. We chose a treatment selection rule to minimise the risks of dropping potentially effective tVNS treatments or selecting ineffective treatments at an interim analysis. A tVNS treatment will be selected to progress to stage 2 if the test statistic is >0.792 (corresponding to a 1-point ULFM mean difference in change compared with a shared control arm; 0.18 of the expected SD of 5.5^11^ and one-third of our targeted MCID). Such a small effect observed halfway through the trial will be very unlikely to improve close to or beyond our targeted MCID even if the treatment is carried forward until the end. Thus, we will drop a tVNS treatment early if it fails to demonstrate an effect of>1/3 of the MCID. At the end of stage 2, a treatment will be declared efficacious if the test statistic is above 2.176—chosen to guarantee that the chance of incorrectly rejecting at least one null hypothesis is controlled at 2.5% (one-sided tests).^23^ See Section 11.1 of the protocol for details on sample size with rationale and aspects of interim analysis including adaptation decision rules with rationale and operating characteristics of the adaptive design.

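### Cheap improvement, not an error: a step-down rule for the second active arm (1.96 once the other arm has passed 2.176) adds power at the same 2.5% family-wise error

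*Protocol article*

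**What the plan says.** Two active tVNS arms are compared with a shared sham arm. The sample size section states its basis as "This assumes a 1:1:1 allocation ratio, 85% marginal power and 2.5% one-sided family-wise type I error". The target is that active treatment should "improve the ULFM by 3 points more than sham tVNS and rehabilitation to be clinically meaningful". The drop threshold of 0.792 is a 1-point "mean difference in change compared with a shared control arm", put at "0.18 of the expected SD of 5.5". The interim takes place with 38 per group and the final analysis with 76 per group. An arm that does not exceed 0.792 at the interim is dropped. At the end, "a treatment will be declared efficacious if the test statistic is above 2.176", a value chosen so that the chance of at least one false rejection is 2.5% one-sided.

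The final rule does not depend on the other arm's result, and the article mentions no closed or step-down test. The Trial design section says early stopping for efficacy is not part of the design, so continuing arms are judged together at the end of stage 2. The Primary outcome section promises multiplicity-adjusted confidence intervals and p values without naming the method.

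**The concern.** The value 2.176 protects against the case in which both null hypotheses are true. It is the critical value for the larger of two correlated statistics, given the drop rule. Once one arm exceeds it, the joint null is rejected. By the closure principle the other continuing arm then needs only its own test at 2.5%. The written rule still asks for 2.176, so a second regimen with a final statistic between 1.96 and 2.176 is declared not efficacious although the promised error control would allow the claim. The design may carry both regimens to stage 2, so the situation can arise. What is at stake is power for the second arm. The validity of the trial is not in question.

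**Working it through.** **Inputs** (all from the sample size section): SD 5.5; target difference 3 points; 38 per arm at the interim and 76 at the end; drop unless Z1 > 0.792; final boundary 2.176; 1:1:1 allocation with a shared control. The model is four jointly normal statistics, with correlation 0.5 between arms (shared control, equal allocation) and √(38/76) = √0.5 = 0.707 between stages within an arm. The drop rule is treated as binding.

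**1. The plan's own figures.**
- Interim standard error: 5.5 × √(2/38) = 1.262. One point gives 1/1.262 = 0.7925, matching 0.792.
- Final standard error: 5.5 × √(2/76) = 0.892.
- Family-wise error when both nulls are true is 2 × P(Z1 > 0.792, Z2 > 2.176) − P(both arms rejected) = 2 × 0.01347 − 0.00193 = 0.0250. Solving for exactly 2.5% gives 2.1761.
- Marginal power at 3 points uses means of 3/1.262 = 2.378 (interim) and 3/0.892 = 3.362 (final). P(Z1 > 0.792, Z2 > 2.176) = 86.1%, against 85% stated.

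The plan's figures therefore hold.

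**2. Slack in the written rule.** If one arm works and the other is null, the null arm is rejected with probability P(Z1 > 0.792, Z2 > 2.176) = 1.35%. The guarantee allows 2.5%.

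**3. Step-down rule.** The first step is unchanged: some continuing arm must exceed 2.176. If one does, the other continuing arm is tested at 1.96.
- Both nulls true: the chance of any rejection is fixed by the first step, so it stays at 2.50%.
- One null true: the null arm is rejected with probability at most P(Z1 > 0.792, Z2 > 1.96) = 2.19%, within 2.5%.

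**4. Gain.** An arm gains the probability that it continues with a statistic between 1.96 and 2.176 while the other arm continues and exceeds 2.176.

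Both true effects 3 points, where that probability is 2.2% per arm:
- marginal power: 86.1% + 2.2% = 88.3%
- both declared: 77.2% + 2 × 2.2% ≈ 81.7%
- at least one declared: 86.1% + 86.1% − 77.2% ≈ 94.9%, before and after

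True effects 3 and 2 points:
- weaker arm: 50.0% + 6.2% = 56.2%
- stronger arm: 86.1% + 0.7% = 86.8%

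True effects 3 and 0 points:
- effective arm: 86.1% before and after
- null arm: 1.35% to 2.18%

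A simulation of 4 million trials per scenario agreed with these figures to within 0.1 percentage point.

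**5. Where the extra rejections lie.** Statistics of 1.96 to 2.176 correspond to observed differences of 1.96 × 0.892 = 1.75 to 2.176 × 0.892 = 1.94 points.

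**The case against.** The strongest reply is that nothing here is wrong. Single-step testing against a shared control is a valid choice, and the design meets every operating characteristic it states. That stands, and it is why this is an improvement and not a correction.

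Several other replies also stand:
- **Narrow gain.** Both arms must pass the interim, one must exceed 2.176 and the other must fall just short of it. With both effects at 3 points this changes the conclusion in about 4.4% of trials (81.7 − 77.2, from unrounded values).
- **Size of the effects concerned.** The added declarations have observed differences of 1.75 to 1.94 points, below the 3 points that the protocol article calls clinically meaningful.
- **Agreement of test and interval.** The present rule keeps the decision, the simultaneous interval and the adjusted p value aligned. That is a legitimate reason to prefer it.
- **Unseen documents.** Section 11.1 of the full protocol and the SAP are not shown and may already specify a closed test. In that case only the article's wording needs aligning.

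A reader might infer more than this supports. One such reading is that the trial is underpowered or its boundary miscalculated; the reproduced 2.50% and 86.1% rule that out. Another is that the written rule costs about 21 participants. It is true that the single-step rule would need about 83 per arm to reach 81.7% for declaring both arms (3 × 7 = 21 more), but the trial is powered on marginal power, which 76 per arm already delivers. A third is that step-down helps in every scenario. It is never worse, but it leaves the chance of at least one success, and the power of a lone effective arm, unchanged.

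**Conclusion.** The point holds as a cheap improvement. The stated boundary is correct, and requiring it of the second continuing arm after the first has passed is stricter than the 2.5% guarantee needs. The gain is 2.2 percentage points of marginal power and 4.4 points in the chance of declaring both arms if both effects are 3 points, and 6.2 points for the weaker arm if the effects are 3 and 2. The cost in error is a rise from 1.35% to at most 2.19% for a null arm beside an effective one.

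These figures assume SD 5.5, 38 then 76 evaluable per arm, and a binding drop rule. The first step depends on that last assumption under either rule: if dropped arms were carried on and tested, 2.176 would give a family-wise error of 2.73%. The second step at 1.96 does not depend on it. A second-step value of 1.897 would use the full 2.5% but only if dropping is binding, so 1.96 is the safer choice.

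**What to change.** Before any unblinded data are accessed, change the final rule in the protocol and SAP to:

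*A continuing arm is declared efficacious if its statistic exceeds 2.176. If one arm does so, the other continuing arm is declared efficacious if its statistic exceeds 1.96. If only one arm continues, it needs 2.176.*

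Report step-down (closed-test) adjusted p values so that they agree with the decision. Keep the single-step simultaneous confidence intervals for estimation, with a note that the second arm's interval may just include zero although its test rejects.

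No extra participants are needed. The costs are the higher error on a null second arm given above, the possible mismatch between test and interval, and perhaps a formal amendment. The Ethics and dissemination section requires agreement of the steering committee, funder and ethics committee for significant design changes. Recruitment began on 30 November 2023 and the article does not show how near the interim is, so the team should first confirm that the change can still be made blind. If it cannot, the present rule remains valid and should stay.
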